### Data Collection

The initial part of the questionnaire consists of questions about the patient’s demographic data and data on the patient’s support from the medical staff. The first part of the questionnaire will cover the assessment of self-care. Self-care in patients with type 2 diabetes will be assessed using the SCODI instrument [39]. The tool consists of 40 assumptions classified into 4 dimensions: self-care maintenance (12 assumptions), self-care implementation (8 assumptions), self-care monitoring (9 assumptions), and self-confidence (11 assumptions). The instrument is assessed using a Likert scale, where a higher score represents better self-care [39]. We will also use the Brief IPQ scale [40] to assess disease perception. The questionnaire rapidly assesses disease perception and measures the patients’ cognitive and emotional representations of their disease. The questionnaire contains 8 questions graded on a 10-point scale and 1 open-ended question. There are 5 questions that assess the cognitive perceptions of the disease: consequences (point 1), timeline (point 2), personal control (point 3), treatment control (point 4), and identity (point 5); 2 questions that assess emotional representation: care (point 6) and emotions (point 8); and 1 question that estimates the comprehensibility of the disease (point 7). The assessment of causal representation is based on an open response that requires the patients to indicate the 3 most important causal factors in their disease (point 9) [40]. The nurses employed at the family medicine practices will use standardized, calibrated devices according to the guidelines to measure blood sugar, blood pressure, and HbA_1c_ levels and body weight. Data will be recorded at each control check.

The questionnaires were translated using the reverse translation method into English. This ensured the adequacy and consistency of the translated questionnaire. It was first translated from English into Slovene independently by 2 translators. One of the translators involved had expertise in nursing, and the other had the necessary knowledge of the standard English language. Thus, we obtained 2 translation versions, which were merged in the next step through review and consultations. In the last step, 2 experts with the necessary English knowledge translated a standard Slovenian questionnaire into English and combined it into a familiar form. Thus, we obtained 2 translated questionnaires in English, which we subsequently incorporated into a standard format [44,45]. The final version of this translated questionnaire will need to be preconfirmed and tested on a small sample, and the subsequent corrections will be tested on a large representative sample of respondents [46]. We will carry out the validation of the questionnaire. To analyze the reliability of the questionnaire, we will calculate Cronbach α and perform confirmatory factor analysis. Cronbach α measures intrinsic reliability among multiple elements and assesses how reliable the questionnaire responses are [47]. If the Cronbach α value is low (close to 0), it means that some or all of the items do not measure the same dimension [47-49]. The content validation process will consist of the following steps: the preparation of a content review form, selection of an expert review team, implementation of content review, review of domains and elements, determination of the rating for each item, and calculation of Content Validity Index (CVI) [50]. The content validity will be assessed by a nurse employed at the family medicine practice with knowledge of type 2 diabetes self-care. To assess the substantive validity of the questionnaire, we will use the index of substantive validity for individual statements (Item-CVI) and the entire questionnaire (Scale-level CVI). We will use a 4-point scale for evaluation [50]. Item-CVI results higher than 0.78 from 3 or more experts in assessing an individual statement represent good substantive validity [51]. Scale-level CVI results of 0.80 or more indicate good substantive validity [52].

### Inclusion Criteria

A randomized controlled trial will be conducted in family medicine practices where individuals with type 2 diabetes are treated throughout Slovenia. There are 10 regional units of the Health Insurance Institute of Slovenia, with 241 private and 656 public health institutions [53]. The research will cover 1 family medicine practice from each regional unit. According to the data from January to September 2018, there were 28,593 treatments of individuals in connection with type 2 diabetes conducted in family medicine practices [54]. This number was used to calculate the sample size, which was calculated using a sample size calculator (Raosoft) [55] that has been used in many similar health research studies [56-59]. We used a power analysis and entered the necessary data with a 95% error rate and 5% confidence level. The required minimum sample size is 380 participants. We will include individuals aged over 18 years with type 2 diabetes who have already been given treatment. Additionally, there should be no acute complications due to the consequences of type 2 diabetes in the individuals included in the study. They must use a mobile phone and a blood glucose meter during the research period.

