### Statistical Analysis

The sample will be described with descriptive statistics, and the explanatory variables will be presented with frequencies and percentages. In contrast, the numerical variables will be presented with the mean value, SD, and minimum and maximum values. To test the relationship between different variables, we will use the Mann-Whitney *U* test in the case of an uneven distribution of variables or the *t* test of independent samples in an even distribution of variables. The significance level of α=.05 will test the hypotheses.

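### The sample size of 380 is a survey-precision figure presented as a power analysis, so the protocol gives no power basis for its between-group hypotheses

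*Protocol article*

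**What the plan says.** The sample-size rationale is in the protocol article under Methods, Inclusion Criteria. It starts from a national activity count: "there were 28,593 treatments of individuals in connection with type 2 diabetes conducted in family medicine practices". It goes on: "This number was used to calculate the sample size, which was calculated using a sample size calculator (Raosoft"). The method and inputs are then given as "We used a power analysis and entered the necessary data with a 95% error rate and 5% confidence level", and the result as "The required minimum sample size is 380 participants".

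The hypotheses are under Objectives and Hypotheses. There are five, none ranked as primary. Each compares the intervention group with the control group at the first control visit: self-care, illness perception, blood sugar and HbA1c, body weight, and blood pressure. Under Statistical Analysis, the groups are compared by the Mann-Whitney U test or by "the *t* test of independent samples in an even distribution of variables", and "The significance level of α=.05 will test the hypotheses".

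The article gives no target difference, SD, power or allowance for loss to follow-up, and does not name the outcome to which 380 relates.

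**The concern.** A power analysis for a two-group trial links four things: the difference to be detected, the variability of the outcome, the error rates and the number per arm. The inputs named here are a population size, an error rate and a confidence level. Those belong to a survey calculator that answers a different question: how many people to sample to estimate a percentage with a given precision. No hypothesis in this trial is about a percentage in a population of 28,593, and the size of the source population plays no part in sizing a randomised comparison.

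At stake is what the reader is told. The words power analysis and required minimum say that the trial was sized to detect something. If 380 comes from a survey formula, nobody has said what difference the trial can detect, or whether that difference would matter to patients.

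**Working it through.** **Step 1. Reproduce 380.**

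Inputs: N = 28,593 (Inclusion Criteria); margin E = 5% and confidence 95% (the two stated percentages with their labels exchanged); proportion p = 50% (assumed, not stated in the article).

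Precision formula for one proportion with finite-population correction, in percentage units:

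- x = z² · p · (100 − p) = 1.96² × 50 × 50 = 9,604
- n = N·x / [(N − 1)·E² + x] = 28,593 × 9,604 / (28,592 × 25 + 9,604) = 274,607,172 / 724,404 = 379.08, rounded up to **380**

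This matches the stated figure exactly. The formula contains no treatment effect, SD, second group or power.

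**Step 2. Inputs as literally printed.**

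With a 95% margin and 5% confidence (z = 0.0627), the same formula gives n of about 0.001. So the calculator must have received 95% confidence and a 5% margin, and the labels were transposed in the text. The number is unaffected.

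**Step 3. Does the population count matter?**

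The article's figure counts treatments, not people. With N = 20,000 the formula gives 376.9 (377), and with N = 50,000 it gives 381.2 (382). Counting people instead would hardly move the result within that range.

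**Step 4. What 380 delivers for the planned comparison.**

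Assumptions, none stated in the article: 1:1 allocation (190 per arm), two-sided testing at 0.05, and the t-test branch of the analysis. Power is from the noncentral t distribution with 2n − 2 degrees of freedom and noncentrality d·√(n/2), where n is the number per arm and d the difference in SD units.

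| Standardised difference d | Power, 190 per arm |
|---|---|
| 0.10 | 16% |
| 0.20 | 49% |
| 0.25 | 68% |
| 0.30 | 83% |
| 0.40 | 97% |
| 0.50 | 99.8% |

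Detectable difference:

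- 80% power: d = 0.288. Normal approximation as a check: (1.960 + 0.842) × √(2/190) = 0.287.
- 90% power: d = 0.333.
- With 15% lost (assumption), 190 × 0.85 = 161.5 per arm: d = 0.313 at 80% power.
- One-sided test at 0.05 instead, no loss: d = 0.256 at 80% power, and 62% power at d = 0.20.

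Total needed for 80% power, two-sided: 788 at d = 0.20 and 128 at d = 0.50. So 380 could be about half of what is needed (380/788 = 0.48) or about three times it (380/128 = 2.97), depending on a target difference that the article does not give.

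**The case against.** **An article condenses, and a fuller plan may hold the power calculation.** This would answer an omission, but the article does set out its sample-size basis: the calculator, the population, the inputs, the name of the method and the result. What it sets out is not a power analysis, and no other document can make that paragraph correct.

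**The number may be perfectly adequate.** This stands. A reader might infer that the trial is underpowered, but the article does not support that: 380 has 80% power at a standardised difference of about 0.29 and 97% at 0.40, under the assumptions above. What is shown is a missing justification.

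**A null result could still be read.** This also stands. A reader might infer that a null finding on self-care or HbA1c would be uninterpretable. It would not be: the estimate and its confidence interval depend on the data obtained, not on whether a target difference was set beforehand. What is lost is the ability to say in advance which differences the trial could be expected to detect.

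**The transposed labels and the treatments count are slips.** Agreed. The first leaves 380 unchanged and the second barely moves it. Correcting both would still leave a survey calculation under the wrong name.

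**The power figures rest on unstated choices.** True. Allocation is described only as simple randomisation with the same opportunity for all, and sidedness is not given while the hypotheses are directional. The Mann-Whitney alternative is not covered by these figures.

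**Conclusion.** The point holds as a matter of method and labelling; the arithmetic behind 380 is sound for the question that the calculator answers. The stated minimum is the survey-precision size for one proportion (379.08, rounded up to 380, with p = 50% assumed), and the article gives no power basis for any of its five between-group hypotheses.

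On the assumptions of 1:1 allocation, two-sided alpha 0.05 and a t test, the trial as sized can detect a standardised difference of about 0.29 with 80% power, or 0.31 if 15% are lost. A one-sided test would lower the first figure to about 0.26. Whether such a difference is worth detecting cannot be judged from the article.

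The paragraph needs correcting because it claims a property that the calculation does not provide. The swapped labels and the use of treatments in place of people are minor and should be tidied in the same edit.

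**What to change.** Keep 380 as the planned enrolment. In Inclusion Criteria, remove the description as a power analysis, the description as a required minimum, the transposed percentages and the population basis.

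Replace them with a statement of what 380 delivers. The sponsor first has to settle the outcome and score to which it applies, the sidedness of the test and the allocation ratio. Self-care on the SCODI, under Objective 1, fits the stated aim. Because Data Collection describes four SCODI dimensions and no single total, the score must be named.

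Suggested text, if 1:1 allocation, a two-sided test and the t test are confirmed:

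> With 380 participants randomised (about 190 per arm), the trial has 80% power at a two-sided significance level of 0.05 to detect a standardised difference of 0.29 in [named outcome and score], or 0.31 if 15% are lost to follow-up.

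Then convert that difference to score points with an SD the sponsor can support, and say whether it is worthwhile. That last sentence is needed: quoting the difference that 380 happens to detect discloses the trial's sensitivity but does not by itself justify the size.

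The cost is one rewritten paragraph and no extra patients. The downside is a less favourable but accurate statement: about 49% power at a standardised difference of 0.20, and 83% at 0.30.

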### Statistical Analysis

The sample will be described with descriptive statistics, and the explanatory variables will be presented with frequencies and percentages. In contrast, the numerical variables will be presented with the mean value, SD, and minimum and maximum values. To test the relationship between different variables, we will use the Mann-Whitney *U* test in the case of an uneven distribution of variables or the *t* test of independent samples in an even distribution of variables. The significance level of α=.05 will test the hypotheses.

### Ethics Approval

We received permission from The Republic of Slovenia National Medical Ethics Committee (03/5R-2021) for the primary research. We will also obtain the necessary consent from all institutions and participants in a randomized controlled trial. We will obtain permits from the institutions to enter the family medicine practices to conduct the research. We will also obtain consent from the participants to participate in the study. Before starting the analysis, we received written authorization to use the mobile app *forDiabetes* [36]. We also obtained permission from the authors to use and translate the questionnaires SCODI [39] and Brief IPQ [40]. In the introductory part of the research, the research participants will be acquainted with the purpose and goal of the study, ensuring the anonymity of the participants, voluntary nature of participation, and possibility of withdrawing from participation. Participants who submit a completed questionnaire will consent to the research and use of their data. The data will be securely stored and used only for research and publication, and only the researchers involved will have access to the actual data. The data will be kept for 10 years. We will ensure the anonymity of the participants throughout the research; it will not be possible to identify a person and institution or other demographic data from the results presented. The study does not pose a risk to the participants and represents a minimal burden. We will also consider the principles of legality, fairness, proportionality, accuracy, and timeliness of the data during the research

## Results

Before the current phase of the research, we have prepared a translation of the mobile app that will be used by the participants of the intervention group, as well as more detailed instructions for using the app. We have also prepared a translation of the questionnaires in Slovene. The research results will be published in 2023.

## Discussion

### Expected Findings

Adherence to chronic management measures is essential for maintaining good health outcomes [60]. By 2045, the number of patients with diabetes will rise to approximately 629 million [61]. Mobile apps provide motivation and support for self-care in these patients [62], but there is still a lack of knowledge about their actual use [63].

Based on the described methodological process, we will perform a randomized controlled trial to determine the effectiveness of a mobile app and its impact on patients with diabetes. The research represents a unique opportunity to use and integrate mobile apps in the treatments of individuals with type 2 diabetes to solve challenges and achieve better self-care. We will enable the use of an efficient and evidence-based mobile app that is suitable for users’ needs and includes the concept of self-care in the framework of mobile health. The research will help to gain new knowledge in integrating mobile technology into the life of an individual with type 2 diabetes.

### Limitations

The main limitation is that we will only include patients with controlled and managed type 2 diabetes in the study, which means that we will examine only a specific part of the population. The study will also have only patients treated in family medicine practices, which may prevent the possibility of generalization to all people with type 2 diabetes. 

Having both control and intervention groups at the same family medicine practices may provide bias, as this will not conceal the allocation of an intervention in a randomized controlled trial. Researchers will know in which group the participants were assigned, as these participants will carry out the necessary training for the use of the mobile app and other interventions. The research will use a questionnaire to assess the participants’ self-care and perception of the disease, which can provide socially expected and desirable answers.

Our study contains the following assumptions. People with type 2 diabetes have deviations or shortcomings in each concept of self-care. The app will affect a patient’s self-care with type 2 diabetes and other critical clinical measures. Self-care and disease perception are measurable and that the translated questionnaire will be helpful in our research. Medical professionals, employees in family medicine practices, and individuals with type 2 diabetes will be willing to participate in the study. People with type 2 diabetes will actively use the mobile app and monitor their health through data entry. The results expected during the study are changes in self-care; disease perception; blood sugar, blood pressure, and HbA_1c_ levels; and measured body weight.

## Abbreviations

Brief IPQ: Brief Illness Perception Questionnaire
CVI: Content Validity Index
HbA_1c_: glycated hemoglobin
SCODI: Self-Care of Diabetes Inventory
